**Intervention groups**

| Week | Measure | Content of MBI | Content of Focus group |
| --- | --- | --- | --- |
| 0 | V | N/A | N/A |
|  |  | Introduction to MBI group  Body scan  Mindful eating | Introduction to Focus group  Discussion on the definition and content of job stain |
|  |  | The association between thought and feeling  Sitting meditation  Discussion on homework exercises | Discussion on the work stressors  Finding out the possible solutions for job strain |
|  |  | Visual and sound meditation  Walking meditation  Discussion on homework exercises | Developing available strategies to enhance workers’ mental health  Redesigning work content  Inviting the management into groups, if applicable |
|  | V | Mountain meditation  Yoga  Discussion on homework exercises | Developing available strategies to enhance workers’ mental health  Redesigning work content  Generating new ideas about stress management  Inviting the management into groups, if applicable |
|  |  | Dealing with difficult situations with mindfulness  Breathing exercise  Discussion on homework exercises | Developing available strategies to enhance workers’ mental health  Generating new ideas about stress management  Inviting the management into groups, if applicable |
|  |  | Loving-kindness meditation  One minute or three minutes of mindful breathing  Discussion on homework exercises | Conducing the program  Monitoring the process |
|  |  | Choiceless awareness meditation  Breathing exercise  Discussion on homework exercises | Conducing the program  Monitoring the process |
|  | V | Integration  Mindfulness of daily activities  Building a better relationship with yourself | Integration and reviewing |
| 12 | V | N/A | N/A |
| 16 | V | N/A | N/A |

Measures

The survey questionnaire will compose of five parts: personal data, Chinese Health Questionnaire, prolonged fatigue, Job Content Questionnaire, and Perceived stress.

**Chinese Health Questionnaire.** Psychological distress will be measured by the Chinese Health Questionnaire (CHQ-12), a well-validated instrument (Cheng & Williams, 1986; Chen et al., 2000). The CHQ-12 was adapted from the General Health Questionnaire (Goldberg, 1978) with culturally relevant modification. The twelve items in the questionnaire, including questions pertaining to depression, anxiety, sleep disturbance, somatic concerns, and interpersonal difficulties, were on a four-point Likert scale. A higher score indicated a high level of psychological distress.

**Checklist Individual Strength questionnaire.** The Checklist Individual Strength questionnaire (CIS), which confirmed discriminant validity and convergent validity, will be used to measure prolonged fatigue (Beurskens et al., 2000). The CIS was developed to assess the extent of the subjective fatigue, reduction in motivation, reduction in activity, and reduction in concentration. The CIS consists of 20 items on a 7-point Likert scale ranging from 1 to 7. A higher score represented a higher level of prolonged fatigue.

**Job Content Questionnaire.** The Job Content Questionnaire (JCQ) (Karasek, 1985) is a commonly used questionnaire to assess job control (including 6 items pertaining to skill discretion and 3 items pertaining to decision authority), job demands (5 items), and workplace social support (8 items). The translated Chinese version of the JCQ was reported to have acceptable psychometric properties and will be adopted in the study. For the purpose of the study, only the subscales of job control and job demands will be obtained. A higher-sum score represents a higher level of job control or job demands.

**Perceived stress.** The 10-item Perceived Stress Scale (PSS-10) developed by Cohen and his colleagues will be adopted to measure a global level of perceived stress (Cohen, et al, 1983). Participants will be asked to respond to each question on a 5-point Likert scale ranging from 0 (never) to 4 (very often). A higher total score indicates a higher level of uncontrollable, unpredictable, and overwhelming feelings.

Statistical analysis

The percentages of personal characteristics of the participants will be presented. The comparisons between Group M and Group C-M and between Group F and Group C-F will be conducted separately using the chi-square test or Student’s t-test. The general linear model will incorporate repeated measures: a two-way mixed design ANOVA will be performed individually to determine the interactive effects and then the simple main effects of each intervention and the five continuous time points for the measured dependent variables. In addition, in order to explore the influences of personal characteristics on the outcomes of each intervention with time respectively, the interaction and simple main effects of time by gender, age, education, and occupation on the measured dependent variables will be analyzed as well.

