Effects of mindfulness based stress reduction and focus group on dealing with job stress and emotional disturbance: a longitudinal study with randomized quasi experimental design

| Abstract  Mindfulness-based intervention (MBI) is a newly psychotherapy program. It has been evidenced to be beneficial for decreasing pain, sleep problems, stress reactions, and emotional disturbance. Knowledge of the benefit of MBI to job stress is little. Focus group is a good way to obtain a great amount of relevant information regarding with the discussed issues in a short time. However, the systematic evaluation of the effects of Focus group applying at workplace is limited. The aims of the study are (1) to explore the effects of MBI and Focus group on job stress and workers’ psychological problems, (2) to examine the influence of workers’ characteristic (gender, age, and occupation) on the effects of MBI and Focus group.  The study will adopt a longitudinal research design with randomized quasi- experimental trial. Four companies are chosen for the study. The workers at high risk for mental distress provided by the company will be invited to take part in the study. The participants from two of four companies will be randomly assigned to MBI (Group M) or the waiting-mindfulness-list control group (Group C-M). The participants from the other two companies will be randomly assigned to Focus group (Group F) or the waiting–focus-list control group (Group C-F). One hundred members will be recruited in each group. Longitudinal Data will be collected five times at pre-, during, post- the intervention and follow-up twice with a four-week interval between measurements.  The research questionnaire will include basic information, Chinese Health Questionnaire, Checklist Individual Strength Questionnaire, and Perceived Stress Scale, Job content Questionnaire. All the questionnaires are validated instruments. SPSS-13.0 will be used for statistical analysis. Repeated measure will be adopted to examine the effects between pre- and post- interventions on job stress and emotional disturbance. The comparisons between the intervention group (Group I) and the waiting-list control group (Group C) will be conducted using the chi-square test or Student’s t-test. The general linear model will incorporate repeated measures: a two-way mixed design ANOVA will be performed to determine the interactive effects and then the simple main effects of intervention and the five continuous time points for the measured dependent variables. In addition, in order to explore the influences of personal characteristics on the outcomes of the intervention with time, the interaction and simple main effects of time by gender, age, education, and occupation on the measured dependent variables will be analyzed as well.  Keywords: workplace health program; mental health; job stress |

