**Method**

Study design and the participant

The study will adopt a randomized controlled study design. Four manufacturing factories are chosen for this study. All the full-time workers in the factories will be requested to fill out a questionnaire regarding mental health and job content. The screening procedure was approved by the Institutional Review Board of the Changhua Christian Hospital. After pre-interventions assessment, the workers with psychological distress and job strain would be invited to participant in the study. The workers who are willing to take part in the study will need to give their informed consent and will be the participants for the study. The participants from two of four companies would be allocated into the MBI group (Group M) or the waiting-mindfulness-list control group (Group C-M) by block randomization. The participants from the other two companies will be randomly allocated to Focus group (Group F) or waiting-Focus-list control group (Group C-F). Each group is expected to have about 100 participants. The real number of participants in each group will be depended on how many workers are willing to take part in the study.

Study procedure

After pre-interventions assessment, the workers with psychological distress and job strain would be invited to participant in the study. All the participants will to need to give their written informed content to the research team. The researchers will assign the participants into the intervention groups or control groups by block randomization. After randomization, two well-trained research assistants will notify each participant about the group he or she will take part. The intervention groups will be led by the relevant experts. The contents of the interventions are list below. All the participants would be measured five times with an interval of four weeks between measurements. These measurements will be taken at pre-intervention (T1), at mid-intervention (T2), at the completion of intervention (T3), four weeks after intervention (T4), and eight weeks after intervention (T5). The research assistants will distribute and collect the questionnaire.

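### The repeated-measures ANOVA fixed in the protocol turns the main longitudinal analysis into a complete-case analysis; a mixed model would keep all observed data

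*Protocol*

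**What the plan says.** The Statistical analysis section of the protocol names the model for the longitudinal outcomes: "The general linear model will incorporate repeated measures: a two-way mixed design ANOVA will be performed individually". Its purpose is "to determine the interactive effects and then the simple main effects of each intervention and the five continuous time points". The preceding sentence says that the chi-square and t-test comparisons "between Group M and Group C-M and between Group F and Group C-F will be conducted separately".

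The Abstract describes the same model and adds "SPSS-13.0 will be used for statistical analysis". Under Study procedure, "All the participants would be measured five times with an interval of four weeks between measurements": T1 before the intervention, T2 midway, T3 at completion, T4 and T5 four and eight weeks later.

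On size, Study design says "Each group is expected to have about 100 participants", followed by "The real number of participants in each group will be depended on how many workers are willing to take part in the study". The ethics application form attached to the protocol gives a total of 400 and describes the trial as open with a waiting-list comparator. The document gives no expected rate of missed measurements.

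**The concern.** A two-way mixed-design ANOVA fitted as a repeated-measures GLM takes one row per worker with all five scores. A row with a gap is left out of the model for that outcome, so one missed occasion also discards the worker's four observed scores. The exclusion works outcome by outcome, and the separate t-tests and chi-square tests are not affected. The model that carries the arm-by-time question is affected.

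Two things are at stake. The first is precision, because observed data are thrown away on top of the data that are truly missing. The second is bias, because having all five scores is determined after randomisation. One arm attends a weekly programme and the other waits, both unblinded, so the reasons for missing an occasion may differ between arms.

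**Working it through.** **Inputs.** From the protocol: about 100 per arm, five occasions, two arms per comparison. The total agrees: 4 × 100 = 400. It cannot be derived further, because no alpha, power, effect size, SD or dropout rate is given. Assumed here: T1 complete (it is the pre-intervention assessment), two-sided 5%, SD = 1, and the missingness rates and correlations shown below.

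**1. Workers kept, intermittent misses.** With independent non-response m at each of T2 to T5, the share kept is (1 − m)^4 and the share of records truly missing is 4m/5.

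| m | kept per 100 | workers dropped | records missing | ratio |
|---|---|---|---|---|
| 5% | 0.95^4 → 81.5 | 18.5% | 4.0% | 4.6 |
| 10% | 0.90^4 → 65.6 | 34.4% | 8.0% | 4.3 |
| 15% | 0.85^4 → 52.2 | 47.8% | 12.0% | 4.0 |

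**2. Workers lost, permanent dropout.** If 20% leave, spread evenly over T2 to T5, the share missing at T1 to T5 is 0, 5, 10, 15 and 20%, a mean of 10%. The ratio is 20/10 = 2.0. If all 20% leave before T2, records missing are 4/5 × 20% = 16% and the ratio is 20/16 = 1.25.

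**3. Power of the arm-by-time F test.** Assume true differences of 0, 0.15, 0.3, 0.3 and 0.3 SD at T1 to T5 and equal correlation r = 0.6. The mean difference is 0.21, and the squared deviations sum to 0.0441 + 0.0036 + 3 × 0.0081 = 0.072. The non-centrality is (n/2) × 0.072/(1 − 0.6) = 0.09n, with 4 and 4(2n − 2) degrees of freedom.

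- n = 100 (nothing missing): 9.0, power 66%.
- n = 90 (approximating a model that uses all observed data at m = 10%): 8.1, power 61%.
- n = 66 (complete cases at m = 10%): 5.94, power 46% (46% to 47% by simulation).

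The comparison that isolates the choice of method is 61% against about 47%. The step from 66% to 61% is the cost of the missing data themselves, which no model restores.

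**4. Bias in a severe scenario.** Assume no true effect. After T2, 40% of intervention workers above the T2 mean drop out, against 10% of all others. Half of a standard normal lies on each side of its mean, with means ±0.798.

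- Share of the intervention arm kept: 0.5 × 0.9 + 0.5 × 0.6 = 0.75.
- Completers' T2 mean: 0.5 × 0.798 × (0.6 − 0.9)/0.75 = −0.160 SD.
- At any other occasion, with r = 0.6: 0.6 × (−0.160) = −0.096 SD.
- Control completers: expected mean 0, because dropout there is unrelated to score.

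The between-arm difference at T3 to T5 is therefore about −0.10 SD, where lower is better for distress, fatigue and stress. T1 shows the same −0.096, so the change from T1 to T3–T5 is about 0 (about 0.03 SD in favour of control if correlation is serial at 0.75). With 20% in place of 40%, the T3 to T5 bias is about −0.03 SD. With the same dropout pattern in both arms it is zero.

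**5. Sphericity (secondary).** By simulation with 100 per arm, no effect and serial correlation 0.75, type I error of the interaction test is about 7.5% uncorrected, and about 5% with the Greenhouse-Geisser correction or the multivariate test. With equal correlations there is no inflation.

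**The case against.** The strongest reply is that missing-data handling, analysis sets and sphericity corrections commonly belong in a statistical analysis plan, and that plan is not shown. Listwise exclusion is a property of the named procedure, not a sentence in the protocol. An unseen plan could add imputation. Research assistants hand out and collect the questionnaires, so few may be missed.

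That is fair as to size, and the figures are conditional for that reason. It does not remove the point, because the protocol chooses the model itself. A later plan would have to replace or supplement that model.

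Four stronger readings are tempting and are not supported:

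- **The test relies on sphericity and exceeds 5%.** The protocol does not commit to the uncorrected F test. The Greenhouse-Geisser and multivariate tests come with the same procedure.
- **The analysis abandons the randomised comparison.** Arm by time does compare randomised arms. What changes is who is included.
- **The interaction test carries the 0.10 SD bias.** In the scenario above, that bias falls on the between-arm simple effects. The contrast with T1 nearly cancels it, leaving mainly a distortion at T2 (−0.160 + 0.096 = −0.064 SD).
- **Four to five times as much is always lost as is missing.** This holds only for intermittent misses. Under permanent loss of 10% at each occasion, only about 66 per arm are observed at T5 whichever model is used.

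**Conclusion.** The point holds in a limited form and is worth acting on. As normally run, the model fixed in the protocol is a complete-case analysis for each outcome. With intermittent non-response of 5% to 15% per occasion, it keeps about 81 to 52 of 100 workers per arm. At 10%, it gives up about 14 percentage points of power (61% to 47%) for an assumed 0.3 SD effect at r = 0.6. With permanent dropout, the excess loss is only 1.25 to 2 times the missing records.

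Bias is possible, not shown. It reaches about 0.10 SD in the simple between-arm effects only under severe dropout that depends on arm and score. It is near zero for change from T1. All of these rates, effect sizes and correlations are assumptions; the protocol supplies none of them. Sphericity is a side issue.

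**What to change.** In the Statistical analysis section and the Abstract, replace the repeated-measures GLM with a linear mixed model for repeated measures (for example SPSS MIXED), fitted separately for each intervention against its own waiting list. Include arm, time and arm by time, with an unstructured covariance. Use all available observations from all randomised workers in their assigned arm. Either keep T1 as an outcome with a common baseline mean, which also retains workers seen only at T1, or use T1 as a covariate. Such a model removes the bias described above when dropout depends on scores already observed; it does not cover dropout that depends on unobserved scores.

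The unstructured covariance also removes any need for sphericity. If the ANOVA is kept, name the Greenhouse-Geisser or multivariate test in advance.

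The cost is a change of wording and slightly more modelling work. No visit, questionnaire or participant is added.

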**Purpose of the study**

The aims of the study are to determine the effectiveness of MBI and Focus group as a workplace health promotion program on psychological distress, prolonged fatigue, job strain (job control and job demand), and perceived stress and to explore the influences of personal characteristics (including gender, age, education, and occupation) on the outcomes of each intervention with time.

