| Special condition | | - Intense care - Child intense care - Genetic treatment - Prosthetics | | | - Quarantine - Intravenous injection - Controlled drug - Other：________ | | | | - Surgery - CT - Gynecological supplies | |
| Inclusion criteria | | - 18 Years to 65 Years healthy employees with psychological distress and job strain - Full-time paid workers | | | | | | | | |
| Exclusion criteria | | - Age < 18y or > 65y - Part-time workers - The workers are not willing to take part in the study | | | | | | | | |
| Expected adverse event/serious adverse event | | None | | | | | | | | |
| The management of expected adverse event/ serious adverse event | | None | | | | | | | | |
| Recruit subjects | | - Media advertisement（attach the content） - TV - Radio - Newspaper - Internet - Bill board - Poster - Flyers | | | | | ■ Oral introduction   - Other________ | | | |
| Result report or publication | | Publication in academic journals or presentation in conference. | | | | | | | | |
| 1. Is there special protection in getting the informed consent of the vulnerable groups?   □Yes, specify______  □No  ■NA | | | | | | | | | | |
| 1. Is there Data safety monitoring plan, DSMP?   Explanation: except for minimal risk trials, the protocol should have DSMP. The definition of minimal risk: it means the changes or degrees of hazards caused to the body or mind is equivalent to those caused from the daily life of health subjects, conventional medicine, and psychological examination. The hazard does not increase as participating in the human trial.  □ Yes, attach DSMP protocol  ■ No | | | | | | | | | | |

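### Workers appear to be selected on the score that also serves as T1, so the planned pre-post, within-arm time and time-by-characteristic results are open to regression to the mean; the effect should be the T1-adjusted between-arm difference

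*Protocol*

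**What the plan says.** **Selection.** Under Method, the whole full-time workforce is screened: "All the full-time workers in the factories will be requested to fill out a questionnaire regarding mental health and job content". Then: "After pre-interventions assessment, the workers with psychological distress and job strain would be invited to participant in the study". The inclusion criterion in the application form is "18 Years to 65 Years healthy employees with psychological distress and job strain"; no cut-off is given. The outcomes listed under Purpose of the study are "psychological distress, prolonged fatigue, job strain (job control and job demand), and perceived stress", so the domains used to select are also outcomes.

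**Measurements.** Study procedure states: "All the participants would be measured five times with an interval of four weeks between measurements". The first is described thus: "These measurements will be taken at pre-intervention (T1". The schedule under Intervention groups marks one measurement at week 0, before the first session. No second baseline after selection is described.

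**Analysis.** The abstract says: "Repeated measure will be adopted to examine the effects between pre- and post- interventions on job stress and emotional disturbance". The Statistical analysis section plans M v C-M and F v C-F comparisons and a two-way mixed ANOVA, with the interaction first and "then the simple main effects of each intervention and the five continuous time points for the measured dependent variables" after it. It then plans interactions and simple effects of time with gender, age, education and occupation, and states no arm term for these. T1 is nowhere given the role of covariate.

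**The concern.** People chosen because a score is high will on average score lower next time, treated or not, because part of the high score was transient. If the choosing score is kept as T1, every comparison of later visits with T1 inside one arm contains this fall. Three planned analyses are exposed: the abstract's pre-post comparison, the simple effect of time within each arm, and the time-by-characteristic effects. In the last, subgroups that start further from their own mean, or answer less reliably, fall by different amounts, and this can look like a difference in response to the programme.

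The protocol does not say which result is the estimate of effect, nor that within-arm change is only descriptive. A near-certain significant fall in Group M or Group F could therefore be offered as evidence.

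A second, smaller cost comes from treating T1 as one of five outcome levels. The group main effect averages in a visit at which no effect is possible, and the interaction spreads one contrast over four degrees of freedom.

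**Working it through.** The protocol states no power calculation, cut-off, SD or reliability, so there is no figure of its own to reproduce.

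**Inputs.** From the protocol: about 100 per group, five visits four weeks apart, and a 17% prevalence of serious distress (Introduction), used here only as an illustrative selected share. Assumed: selected share q = 0.17 to 0.35; retest correlation r = 0.5 to 0.7, equal between all visits before selection; selection on one normally distributed score; two-sided 5% tests.

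**Step 1: size of the untreated fall.** With selection above c, where P(Z > c) = q, the mean T1 of those selected is φ(c)/q SD above the workforce mean. The expected fall is (1 − r) × φ(c)/q.

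- q = 0.17: c = 0.954, φ(c)/q = 0.2531/0.17 = 1.489. Fall = 0.5 × 1.489 = 0.74 SD (r = 0.5); 0.4 × 1.489 = 0.60 (r = 0.6); 0.3 × 1.489 = 0.45 (r = 0.7).
- q = 0.35: c = 0.385, φ(c)/q = 0.3704/0.35 = 1.058. Fall = 0.53, 0.42 and 0.32 SD.
- Over the wider grid q = 0.10–0.50 and r = 0.5–0.8, the fall runs from 0.88 to 0.16 SD.

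**Step 2: what a within-arm test makes of it.** Selection cuts the T1 variance to V = 1 + c·λ − λ², with λ = φ(c)/q. For q = 0.17, V = 1 + 0.954 × 1.489 − 1.489² = 0.20. The variance of the change is (1 − r)²V + (1 − r²). At r = 0.6 this is 0.16 × 0.205 + 0.64 = 0.673, SD 0.82. With n = 100, the expected paired t is about 0.595/0.82 × 10 = 7.3.

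**Step 3: error rates with no treatment effect** (simulation, 100 per arm, r = 0.6, T1 = selection score).

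| Test | top 17% | top 35% |
|---|---|---|
| Within-arm T1–T3 | 100% | 99.9% |
| ANOVA time effect | 100% | 100% |
| Group × time interaction | about 5% | about 5% |
| Between-arm, T1-adjusted T2–T5 mean | 5% | 5% |

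The control arm shows the same false fall as the intervention arm. At r = 0.8 and the top 30%, the within-arm rate is still 96–97%. If T1 is instead a fresh measurement taken after selection (q = 0.17, r = 0.7), it is 4.9%.

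**Step 4: power of the randomised comparison.** Assumed true effect 0.15 SD at T2 and 0.3 SD at T3–T5, r = 0.6, 100 per arm. Ranges cover repeated simulation runs.

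| Analysis | top 17% | top 35% |
|---|---|---|
| Group × time interaction | 69–71% | about 70% |
| Group main effect over T1–T5 | 74–75% | 69–71% |
| Unadjusted T2–T5 mean | 81% | 78% |
| T2–T5 mean with T1 as covariate | 88–90% | 87–88% |

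**The case against.** The strongest reply is that the trial has concurrent randomised waiting-list controls. Both arms regress equally in expectation, the interaction is tested first, and the simple effects of intervention at each visit are themselves between-arm contrasts. All of this stands. A reader might infer that regression to the mean will be reported as benefit, or that the trial's efficacy test is biased. The documents do not support that: the interaction and between-arm tests hold their 5% level, and no sentence says efficacy will be claimed from significance in one arm and not in the other. The abstract's pre-post sentence is also followed at once by between-group comparisons, so it may only introduce the repeated-measures model.

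Second, that screening is T1 is an inference. The shared label, the count of five and the single week-0 measurement make it strong. But the protocol never states it, T1 is listed among measurements of participants, and the abstract has the companies supplying the high-risk workers, which is another route of selection. The screening questionnaire is not said to include the fatigue or perceived-stress scales, so those outcomes may be selected only indirectly and would then regress less.

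Third, a reader might infer that power is halved. A loss from about 87–89% to 42–45% does appear for the group main effect, but only if nobody is selected on T1. That contradicts the premise here. Under selection, T1 varies little and correlates only about 0.32–0.37 with later visits, so the loss is about 13 to 19 points.

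Fourth, covariates are often left to the statistical analysis plan, which is not at hand. The point therefore rests on what the protocol does fix: T1 among the outcome levels, and tests of change over time.

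**Conclusion.** The point holds in limited form. If T1 is the selection score, the pre-post, within-arm time and time-by-characteristic results cannot be read as effects of either programme. The untreated fall is about 0.3–0.7 SD (top 17–35% selected, retest correlation 0.5–0.7), and a within-arm test would be significant almost always. If T1 is a new post-selection baseline, this artefact largely disappears, so the protocol needs to say which it is.

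The randomised comparison is valid either way. Its planned form is inefficient: about 70–75% power against 88–90% with T1 as covariate, for the assumed effect and r = 0.6. The selected share, the correlation and the effect size are all assumptions; the direction of both results does not depend on their exact values.

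**What to change.** In the Statistical analysis section:

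- Define the effect of each intervention as the between-arm difference (M v C-M; F v C-F) at T2–T5, from a repeated-measures model or ANCOVA with T1 of the same scale as covariate.
- Label within-arm time effects as descriptive, and do the same for the abstract's pre-post comparison.
- Examine personal characteristics through arm-by-characteristic terms (by time where wanted), not time-by-characteristic alone.

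In Study procedure, state whether T1 is the screening questionnaire or a new baseline after selection, and reconcile this with the abstract's account of how high-risk workers are found.

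These are changes of wording and model; T1 is already collected, so no new data are needed. The price is that within-arm changes, which will look larger, can no longer be offered as evidence of effect.

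### The planned moderator analysis tests time by characteristic without the intervention factor, so it can confound differences in natural course with effect modification

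*Protocol*

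**What the plan says.** The abstract gives the second aim as "to examine the influence of workers’ characteristic (gender, age, and occupation) on the effects of MBI and Focus group". The Purpose of the study section words it more loosely, and adds education: "explore the influences of personal characteristics (including gender, age, education, and occupation) on the outcomes of each intervention with time".

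Under Method, Statistical analysis, the efficacy model is a group-by-time model, run separately for each intervention: "a two-way mixed design ANOVA will be performed individually to determine the interactive effects". The moderator analysis follows. Its purpose is given as "in order to explore the influences of personal characteristics on the outcomes of each intervention with time respectively", and its content as "the interaction and simple main effects of time by gender, age, education, and occupation on the measured dependent variables will be analyzed as well". The abstract names the same terms.

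The intervention factor appears only in the two-way efficacy model. No interaction of group with a characteristic is named anywhere. The text does not say whether the time-by-characteristic model is fitted in the intervention arm only or in both arms together. Each intervention has its own randomised waiting-list arm, with about 100 participants expected per group and five measurements four weeks apart.

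**The concern.** A question about characteristics and the effects of an intervention is a question of effect modification: does the difference between intervention and waiting list vary with gender, age, education or occupation? A time-by-characteristic interaction asks something else, namely whether the levels of a characteristic change differently over the 16 weeks, for whatever reason.

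Change without treatment is plausible in this trial. Workers are invited because they show distress and job strain at the pre-intervention assessment, so some regression to the mean can be expected, and it need not be the same for all kinds of worker. Only the waiting list can remove it.

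The risk runs both ways. The analysis could suggest that a programme suits workers who would have improved anyway, or it could miss a real difference in benefit. It is the only analysis named for one of the two stated aims.

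**Working it through.** The protocol gives no alpha, effect size, SD or correlation for this analysis, so there is no figure of its own to reproduce.

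**What each model estimates.** For a two-level characteristic, let N be the difference in natural change between the levels, and M the difference in intervention effect between them.

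| Data used | Time-by-characteristic contrast |
|---|---|
| Waiting list only | N |
| Intervention arm only | N + M |
| Both arms pooled, 1:1 | (N + N + M)/2 = N + M/2 |
| Intervention minus waiting list (group factor included) | M |

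Only the last row isolates M. This holds for any numerical assumption.

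**Size.** From the protocol: about 100 per arm, five time points. Assumed: two-sided alpha 0.05, 50:50 split, compound symmetry with correlation 0.6, no dropout, and effects phased in as 0, 0.5, 1, 1, 1 times their full size over T1 to T5.

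This profile has mean 0.7, so its squared deviations sum to 0.49 + 0.04 + 3 × 0.09 = 0.80. For a full-size difference d between levels of size a and b, the 4-df F-test has noncentrality

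λ = d² × 0.80 / [(1 − 0.6)(1/a + 1/b)].

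- Pooled, a = b = 100: λ = 0.80 d² / (0.4 × 0.02) = 100 d².
- Intervention arm only, a = b = 50: λ = 0.80 d² / (0.4 × 0.04) = 50 d².

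With M = 0, so d = N:

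| N (SD) | λ pooled | λ within arm | False moderation, pooled | False moderation, within arm | Group factor included |
|---|---|---|---|---|---|
| 0 | 0 | 0 | about 5% | about 5% | about 5% |
| 0.1 | 1.0 | 0.5 | 11% | 8% | about 5% |
| 0.3 | 9.0 | 4.5 | 65% | 37% | about 5% |
| 0.5 | 25.0 | 12.5 | 99% | 83% | about 5% |

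The percentages are simulated. The noncentral F distribution gives values within about 2 percentage points. At correlation 0.5, N of 0.2 to 0.5 SD gives 24% to 96% pooled and 15% to 71% within arm, so the pattern does not hang on the choice of 0.6.

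**The reverse error.** The pooled contrast vanishes when N = −M/2, and the within-arm contrast when N = −M. At correlation 0.5 with M = 0.4 SD, the pooled test rejects in 5% of trials at N = −0.2, and the within-arm test in 4% at N = −0.4. The group × time × characteristic F-test rejects in 26% to 27% in both cases.

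**Choice of replacement test.** Take M = 0.5 SD (effect 0.5 v 0 SD) and correlation 0.6.

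- Group × time × characteristic, 4 df: four cells of 50 give λ = 0.80 × 0.25 / (0.4 × 4/50) = 6.25, and power of about 48%.
- Group × characteristic on the mean of T3 to T5 adjusted for T1, 1 df: residual variance 0.6 + 0.4/3 − 0.6² = 0.373; SE = √(0.373 × 4/50) = 0.173; 0.5/0.173 = 2.89; power about 82%.

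Both target M, but they are not equivalent tests.

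**The case against.** The best defence is that the Purpose and Statistical analysis sections speak of outcomes over time, not of effects, and call the work exploratory. On that reading, describing trajectories by characteristic is close to what is promised. The sentence also follows directly on the group-by-time model and may be shorthand for extending it. This ambiguity is real, and it lowers the weight of the point. It does not remove it: the abstract says effects, and the interaction is named in both places without group.

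It is also fair to say that the error depends on a natural-course difference the documents do not quantify. At 0.1 SD it is small, and at zero there is none. With no such difference, the within-arm test even has more power (81%) than the three-way F-test (48%) for M = 0.5 SD. That advantage lasts only while the natural course can be taken as equal, which is the assumption the waiting list exists to avoid.

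A reader might infer more than the documents support:

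- That the trial will report natural-course differences as moderation. The documents show only that it can.
- That adding the group factor lifts power from 5% to about 80%. That compares different kinds of test, in a scenario where N = −0.25 SD exactly cancels half of M = 0.5 SD. On the planned ANOVA, adding group gives about 48%; the rest comes from baseline adjustment and averaging T3 to T5.
- That the efficacy result is compromised. The randomised group-by-time comparison does not use this term.

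**Conclusion.** The point holds as a mismatch between an aim and the term chosen to answer it. It is not a detail left to a statistical analysis plan, because the protocol names the interaction and names one without the intervention. Whichever arms are used, the contrast mixes N with all or half of M.

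That conclusion needs no numerical assumption; its practical size does. Over the assumed range of 0.1 to 0.5 SD, false moderation runs from close to nominal to near certain, as tabulated above, under the stated conditions of a two-level characteristic split 50:50, compound symmetry and no dropout. The figures are illustrations, not predictions for this trial. The analysis is exploratory and leaves the main comparison untouched, so this should be corrected but does not put the trial's primary inference in doubt.

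**What to change.** Replace the moderator sentence under Statistical analysis, and its counterpart in the abstract, with text such as:

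*For each intervention separately, effect modification will be tested in a model containing both the intervention arm and its waiting-list arm, by the group × characteristic interaction on the mean of T3 to T5 adjusted for T1, with all lower-order terms and with age kept continuous. Intervention-minus-waiting-list differences with 95% confidence intervals will be shown by level, as exploratory.*

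Name this one test. The group × time × characteristic F-test also targets modification, but it should not be offered as equivalent. The wording of the aim in the abstract and in the Purpose section should be aligned at the same time.

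The cost is wording only: same data, same visits, same participants. The downside is wide intervals and fewer nominally significant results. On a simple change score with 100 per arm, 80% power for the group × characteristic contrast needs 2.80 × √[2(1/50 + 1/50)] = 0.79 SD of change at a 50:50 split, and about 0.99 SD at 20:80, against 2.80 × √(2/100) = 0.40 SD for the main group contrast. Baseline adjustment and averaging improve on this, but modest modification will still often go undetected, which is why the exploratory label belongs in the text.
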